### Study 2: Systems Impact

#### Methods

The evaluation of system-level impact will investigate whether the intervention influences school, municipal, and community systems in ways that support the creation and maintenance of a HPS environment at the 4 intervention sites. This includes (1) measuring changes in school capacity for health promotion, (2) mapping health-promoting actions beyond the health education program, and (3) investigating cooperation and relationships between the municipal health departments, local communities, and schools, as well as identifying unexpected outcomes.

School health promotion capacity will be assessed using the validated Health Promoting School Practices and Capacity Questionnaire (HPS-Q) [75]. This survey consists of 24 items across seven subdimensions: (1) school policies, (2) school ethos, (3) collaboration and involvement, (4) school practice, (5) quality of delivery, (6) physical and financial resources, and (7) school health services. Items related to specific health topics will be adapted to the content of “My Life” following recommendations by Hjort et al [75]. The questionnaire will also include personal characteristics of respondents (gender, age, years working with the target group, years at the workplace, and teaching subjects). To investigate development in health-promoting actions, cooperation and relationships between the municipal health department, local community, and schools, and adverse positive and negative effects, semistructured interviews will be conducted with key actors across intervention schools (Table 2).

#### Data Collection

All school staff working with the involved 10th-grade students will be invited to complete an online survey in SurveyXact [76] to assess changes in HPS capacity. HPS-Q data will be collected at two time points: baseline (April-May 2025 including an additional round for newly employed staff in August 2025) and follow-up (April-May 2026). This period depicts the entire school year, after which students will transition to upper secondary education, employment, or other. System-level changes may first be detected after several years. However, small impacts are expected following the system-level processes integrated into the intervention. To detect these small changes, questions will be added in the HPS-Q survey to assess whether health promotion actions have been developed. The anchoring phase will be assessed; online surveys will be developed specifically for health consultant coordinators, and semistructured interviews will be conducted in April-June 2026 with school- and health consultant coordinators and school and municipal managers across intervention schools (n=16). The interview guides will include themes related to school-municipality collaboration, changes to school practice, unexpected system impacts, and health promotion actions developed as a result of the intervention.

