## Methods

### The “My Life – I Decide” Intervention

The intervention is theoretically inspired by the HPS approach [24], action-oriented teaching [48], the life-psychological method [49], and EOtC [36]. Following common HPS definitions [25], “My Life” uses a whole school approach and operationalizes the 3 HPS components through 4 intervention phases. The phases are: (1) preparation: establishing collaboration between the school and municipal health department and building implementation capacity; (2) planning: adapting the program to schools; (3) health education program: classroom and community-based activities; and (4) anchoring: sustaining health-promoting work at the school. These phases are described in detail below and illustrated in Figure 1 (see also the Template for Intervention Description and Replication [TIDieR] checklist in Checklist 1). Municipal health consultants deliver the intervention in collaboration with school teachers and local actors, aligning with national priorities to strengthen collaboration between the health and educational sectors [46]. The intervention adapts to the school context with preparation and planning taking place before the summer break and school start, while the health education program and anchoring are implemented after the summer break through the full school year. The intervention serves as a framework for HPS practices that can be anchored at the school and further developed over time.

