### Preparation

During the preparation phase, a formal collaboration agreement is established between the school and the municipal health department, outlining roles, responsibilities, political support, and resource commitments. To support implementation, a 2-day training course for health consultants is provided. This covers training in applied didactic methods and the application of the HPS framework. During the training, health consultants receive a comprehensive intervention manual developed to support program implementation. The manual is also provided to the schools for them to understand and be inspired by.

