### Planning

This phase comprises three core activities that focus on organizing and tailoring the program to the local school context.

Establishment of a municipal peer-support network: The network enables health consultants from different municipalities to share experiences and receive backbone support from an experienced health consultant throughout the school year.Start-up meeting between health consultants and 10th-grade teachers at the intervention schools: This meeting is conducted to build a shared understanding of roles and responsibilities during implementation and map already existing and potential collaborations between school and local community actors for the program to build on.Planning meetings for each class: Meetings between teachers and health consultants for intervention school classes are held to tailor the implementation to local conditions.

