### Study Design

Evaluating system-oriented HPS interventions such as “My Life” is challenging due to their multiple target groups, settings, and phases implemented at different organizational levels [51]. Consequently, the evaluation requires multiple context-adaptable designs and methods to address the 3 research objectives [51] (Figure 3). The different designs address the distinct research questions and are analytically complementary, capturing effectiveness, system-level impact, and implementation processes [53]. The evaluation encompassing all 3 research objectives will take place from January 2025 to June 2026. The effectiveness trial (study 1) follows a pragmatic controlled waiting list design with the participating schools as the assigned unit of allocation. Pragmatic trials are designed to determine intervention effects under real-world conditions rather than highly controlled efficacy trials [54]. The design and reporting of the trial are informed by the CONSORT (Consolidated Standards of Reporting Trials) extension for pragmatic trials. Schools are assigned to intervention either in 2025-2026 or 2026-2027. Schools scheduled to receive the intervention in 2026-2027 serve as controls in the trial. The system impact evaluation (study 2) and process evaluation (study 3) acknowledge that HPS interventions are context-bound and are approached through system thinking and realist evaluation. These approaches provide nuanced insights relevant for discussing potential scalability and for understanding outcomes and effects beyond the individual level (Bonell et al [55]: will it work here and for whom?). System-level impact (study 2) is evaluated through a mixed-method design inspired by Pinzon et al [56], while implementation processes at intervention schools (study 3) are examined using an adaptive multimethods design informed by realist evaluation [57], systems thinking [58], and guidance for developing and evaluating complex interventions [51]. The specific methods, data collection, and data analysis used to answer the 3 objectives are explained in detail below and illustrated in Table 2.

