**Figure 3. F3:**
[figure not shown]
Study design of the “My Life” intervention. Green indicates data related to study 1, yellow indicates data related to study 2, and purple indicates data related to study 3. Student- and system-level data related to studies 1 and 2 are collected in both intervention and control schools, whereas data related to study 3 is collected in intervention schools only HPS: health promoting school.

**Table 2. T2:** Overview of data collection activities, timing, purpose, and analytical strategy.

Research objective, focus, and data collection activities	Timing	Purpose	Analytical strategy
1. Student-level outcomes			
Student surveys will be collected at baseline (T0; n≈416); approximately 2‐3 months later at mid-intervention (T1; n≈500), and approximately 4 months after that at follow-up (T2; n≈500)	August 2025-May 2026	To estimate effect changes in student mental and physical health and school well-being	Multilevel mixed models
2. System-level outcomes			
Health promoting school practice and capacity surveys collected among school staff at two time points (n≈70)	April-August 2025; May 2026	To describe differences in school staff health promotion (HP) practices	Pre-post test
Semi-structured interviews with school and municipality coordinators, and school and municipal managers (n=16)	April-June 2026	To identify systems impacts and map system activities, unanticipated outcomes and trace causal pathways across the school systems	The water of systems change [59]; Partnership Synergy Theory [60]
3. Implementation			
Short interviews with health consultant coordinators about the preparation and planning phases	August 2025	To assess implementation degree (high, medium, or low) for each intervention site	
Surveys administered after each health education session and anchoring meetings to health consultants	August-January 2025	To assess fidelity and acceptability of delivering “My Life”	Implementation outcomes [61,62]
3. Mechanisms			
Observations of health education sessions focusing on student engagement (n=20)	August-November 2025	To explore mechanisms of change at the student level	Realist-informed thematic analysis [63]
Semistructured FGIs^a^ with students across all four schools (n=4) and follow-up FGIs (n=4)	November-December 2025	To explore mechanisms of change at the student level	Realist-informed thematic analysis [63]

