#### Analysis Plan

Quantitative survey data will be analyzed descriptively at the school level across the 7 subdomains to capture changes in HPS capacity and practices over time. For each school, mean scores on the 7 subscales and the total HPS score will be calculated at baseline and at follow-up. Change scores will be computed as the mean difference between follow-up and baseline and summarized separately for intervention and control schools.

Qualitative analysis will begin with the transcription of the primary content from the audio recordings generated during the semistructured interviews. Partnership synergy theory [60] will be used as a deductive coding framework to analyze transcripts in relation to municipal-school collaborations. This will be merged with inductive coding, which will explore unexpected system impacts. The transcribed material related to the developed health-promoting actions will be compiled into an action registry in Microsoft Excel, collating data from all 4 intervention sites. This registry will contain: (1) detailed descriptions of each action implemented during the program period, (2) the process of their implementation, and (3) expected system impact. The action registry will be used to depict the relationships between actions and their impacts during the school year. Analysis will proceed in 3 steps. First, we will quantify the actions taken at each study site. Second, we will classify identified impacts according to the Six Core Dimensions of Systems Change [59] to provide a structured typology of system impact. Third, a cross-case comparison [77] will be conducted of the 4 intervention schools supported by site-level findings from the semistructured interviews to identify significant mechanisms across schools that contributed to systems impact [78].

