#### Data Collection

Implementation and mechanism data will be collected across the 4 intervention schools from January 2025 to June 2026, thus covering all 4 intervention phases of “My Life.” For implementation (1), the following data will be collected: short online structured interviews with health consultant coordinators about the Preparation and Planning phases to assess implementation degree, that is, fidelity guided by Proctor et al [61]. Postsession surveys with health consultants will be collected using SurveyXact [76] following each health education session across the eleven intervention classes (n=224) and the anchoring meeting (n=4) (September-January 2025) to capture fidelity and acceptability [61].

For student-level mechanisms (2), the following data will be collected: observations of health education sessions in 6 different classes across the 4 intervention schools (n=23) (August-November 2025) to investigate delivery context and student engagement. Student FGIs will be completed after the health education program in one of the observed classes at each school (n=4) (November-December 2025) to examine perceived relevance and engagement. FGIs will be repeated in the same classes (n=4) (April-May 2026), if HPS actions are implemented in schools to explore how these affect students.

For system-level mechanisms (3), the semistructured interviews described in the systems impact study (study 2) will be used to examine contextual barriers, enablers, and organizational factors influencing implementation and potential scalability (April-June 2026).

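### Both HPS-Q waves can coincide with preparation and planning (intervention schools at baseline, waiting-list schools at follow-up), so the difference in change may be attenuated

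*Protocol article*

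**What the plan says.** The Data Collection section of Study 2 sets the two HPS-Q waves at "baseline (April-May 2025 including an additional round for newly employed staff in August 2025) and follow-up (April-May 2026". Table 2 gives almost the same windows, "April-August 2025; May 2026", with a slightly narrower follow-up.

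The description of the intervention at the start of Methods counts preparation and planning among its four phases, with "preparation and planning taking place before the summer break and school start". In preparation, "a formal collaboration agreement is established between the school and the municipal health department", covering among other things resources and political backing, and the manual is also given to the schools. Planning includes a "Start-up meeting between health consultants and 10th-grade teachers at the intervention schools" and planning meetings for each class.

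On the comparison group, Study Design says: "Schools scheduled to receive the intervention in 2026-2027 serve as controls in the trial". The caption of Figure 3 confirms that Study 2 data come from both groups. The Study 2 Analysis Plan then states: "Change scores will be computed as the mean difference between follow-up and baseline and summarized separately for intervention and control schools".

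Neither overlap between the survey waves and the early phases is mentioned. The Study 2 text describes the interval simply as spanning the whole school year.

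**The concern.** A baseline should precede the intervention, and a control follow-up should precede the controls' own exposure. Here both survey waves sit in spring, which is also when the article's own schedule allows preparation and planning to run: in 2025 for the intervention schools and, by extension, in 2026 for the waiting-list schools.

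The content of these phases overlaps with what the HPS-Q scores. Its subdimensions include school policies, collaboration and involvement, and physical and financial resources. An agreement with the health department, resource commitments and joint meetings with teachers could plausibly move those scores.

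If so, part of the effect is lost from the intervention schools' change, and part of the same effect is added to the controls' change. Both errors pull the difference in the same direction. Change in school capacity is the first of Study 2's listed aims, and the article expects only small impacts. The Potential Challenges section already offers a ready explanation for a weak system-level result, namely that organizational change takes longer than one school year. A muted difference could be put down to that when part of it comes from survey timing.

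**Working it through.** The article states no effect size, standard deviation or power for the HPS-Q, so there is no figure to reproduce. The check is a calendar comparison followed by simple algebra.

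**Step 1: calendar, intervention schools.** Process data are collected "from January 2025 to June 2026, thus covering all 4 intervention phases" (Study 3, Data Collection). With preparation and planning placed before the school year starts, they lie between about January and August 2025. The April-May 2025 wave is inside that window. The August 2025 round for new staff comes at or after its end, and Table 2 schedules the coordinator interviews about these two phases for August 2025.

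**Step 2: calendar, waiting-list schools.** Delivery is in 2026-2027. If the same rule applies, preparation and planning precede the summer of 2026, and the April-May 2026 wave is inside that window. No section dates these activities for the controls, so this step is inferred.

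**Step 3: effect on the difference in change.** Let E be the full effect at follow-up, a the share of E already present in intervention schools at baseline, and b the share present in control schools at follow-up.

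- Intervention change = E − aE = E(1 − a)
- Control change = bE − 0 = bE
- Difference = E(1 − a) − bE = E(1 − a − b)

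The documents give neither a nor b, so the values below are assumptions that show the range.

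| a | b | Intervention change | Control change | Difference |
|---|---|---|---|---|
| 0 | 0 | 1.00E | 0 | 1.00E |
| 0.10 | 0 | 0.90E | 0 | 0.90E |
| 0.10 | 0.10 | 0.90E | 0.10E | 0.80E |
| 0.20 | 0.20 | 0.80E | 0.20E | 0.60E |
| 0.25 | 0.25 | 0.75E | 0.25E | 0.50E |
| 0.30 | 0 | 0.70E | 0 | 0.70E |
| −0.20 | −0.20 | 1.20E | −0.20E | 1.40E |

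The last row shows that the direction rests on an assumption: if preparation temporarily lowered staff ratings, the difference would be inflated.

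**Step 4: the August round.** Suppose a fraction w of intervention baseline responses comes from August with share a₂, and the rest from spring with share a₁. Then a = (1 − w)a₁ + w·a₂. With assumed w = 0.2, a₁ = 0.10 and a₂ = 0.30, a = 0.8 × 0.10 + 0.2 × 0.30 = 0.14. With b = 0.10 the difference is 1 − 0.14 − 0.10 = 0.76 of E, against 0.80 without the August responses. The August round adds to the problem but does not dominate it.

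**The case against.** The strongest case on the other side is that the overlap is possible but not shown. No agreement, manual hand-over, start-up meeting or class meeting carries a date, and the January 2025 to June 2026 window describes data collection. Staff-facing activities could follow the spring survey, which would put a and b near zero. Figures 1 and 3 and the intervention checklist, which could not be seen for this review, may show the timing. This stands, and it is why the point is worded as a possibility.

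Second, much of preparation does not reach the respondents directly. The two-day course is for municipal health consultants, and the agreement is made between institutions. The Anchoring section also ties the building of capacity to actions developed after the health education program. This argues for small shares. It does not make them zero: the intervention overview describes preparation as building implementation capacity, and teachers attend the planning meetings.

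Third, the HPS-Q comparison is descriptive, with no between-group test planned, and Study 2 also draws on interviews and an action registry from the intervention sites. This stands and limits the consequence.

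A reader might go further and infer that the contrast could reverse sign. That needs a + b > 1. If the two shares were equal, preparation and planning would have to account for more than half of the full effect, outweighing the education program and anchoring together. Nothing in the documents supports a share of that size. Nor do they support carrying this point over to the student outcomes, which are measured with a separate survey.

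**Conclusion.** The point holds as a risk of attenuation. The survey windows and the placing of the early phases are fixed in the article, and a later analysis plan cannot move the windows. Following the plan as written, both waves can coincide with preparation and planning, and the reported difference in change can be smaller than the effect of the whole intervention.

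The size is unknown. At assumed shares of 0.10 to 0.25 in both groups the difference would be 0.80E to 0.50E; with no overlap it would be E. The conclusion rests on three assumptions: that staff-facing activities took place before or during the survey waves, that the waiting-list schools follow the same pre-summer schedule in 2026, and that these phases raise HPS-Q scores. The consequence is a misleading description of one system-level outcome.

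**What to change.** 1. In both groups, record for each school the dates of the agreement, manual hand-over, start-up meeting and class planning meetings, and set them against the HPS-Q response dates. This can be done retrospectively.
2. Flag every school and survey round in which a response falls during or after these activities at baseline (intervention schools) or at follow-up (controls).
3. Show the descriptive change scores with and without the flagged schools and rounds. Treat the August 2025 round identically in both groups; removing it from the intervention baseline alone would make the groups differ in how new staff are counted.
4. Where overlap exists, label the result as change from the preparation phase onward, compared with controls that may already have been preparing. State that a small or null difference is then not evidence that system-level impact is absent.

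Moving the control follow-up earlier is not recommended. The window has probably passed, since the abstract reports qualitative collection as completed in June 2026, and an earlier control wave would end concurrent measurement.

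The cost is date logging and one extra descriptive table. The main drawback is a thin clean subset: with about 70 staff and 8 schools, the average is 70/8 = 8.75 staff per school if the 70 covers both groups, so excluding even a few schools leaves little to summarize.

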#### Analysis Plan

Quantitative survey data will be analyzed descriptively at the school level across the 7 subdomains to capture changes in HPS capacity and practices over time. For each school, mean scores on the 7 subscales and the total HPS score will be calculated at baseline and at follow-up. Change scores will be computed as the mean difference between follow-up and baseline and summarized separately for intervention and control schools.

Qualitative analysis will begin with the transcription of the primary content from the audio recordings generated during the semistructured interviews. Partnership synergy theory [60] will be used as a deductive coding framework to analyze transcripts in relation to municipal-school collaborations. This will be merged with inductive coding, which will explore unexpected system impacts. The transcribed material related to the developed health-promoting actions will be compiled into an action registry in Microsoft Excel, collating data from all 4 intervention sites. This registry will contain: (1) detailed descriptions of each action implemented during the program period, (2) the process of their implementation, and (3) expected system impact. The action registry will be used to depict the relationships between actions and their impacts during the school year. Analysis will proceed in 3 steps. First, we will quantify the actions taken at each study site. Second, we will classify identified impacts according to the Six Core Dimensions of Systems Change [59] to provide a structured typology of system impact. Third, a cross-case comparison [77] will be conducted of the 4 intervention schools supported by site-level findings from the semistructured interviews to identify significant mechanisms across schools that contributed to systems impact [78].

